## Abstract

**Objective::**

To assess the effectiveness of paravertebral block for the percutaneous nephrolithotomy (PCNL) patients.

**Method::**

This study will be implemented from May 2021 to March 2022 at Affiliated Hospital of Youjiang Medical University for Nationalities and it was granted through the Research Ethics Committee of Affiliated Hospital of Youjiang Medical University for Nationalities (No.60192038). This study includes a total of 100 patients. The criteria for inclusion of patients involves:

The criteria for exclusion involves:

The visual analogue scores, heart rate, the diastolic and systolic blood pressure, complications, and side effects, the consumption of opioid and extra analgesic needs are recorded in rehabilitation room 1 hour after the surgery and in the first 24 hours of urological service.

**Results::**

Table 1 shows the postoperative data among 2 groups.

**Conclusion::**

In comparison with traditional analgesia, the ultrasound-guided paraventric block is an effective analgesic approach in PCNL, and no additional complications are encountered.

**Trial registration number::**

research registry 6259.

## Introduction

1

Stone disease is a very familiar disorder, uniting all the countries in the world, despite the surgical treatment will be determined by many factors, containing the availability of distinct technologies.^[1,2]^ For urolithiasis, its epidemiology varies on the basis of the prevalence and incidence rate, sex and age distribution, location of stones and composition of stones.^[3,4]^ These differences can be explained by climate, diet and race, among other factors. A review of former epidemiological surveys indicated that the prevalence rate is between 4 percent and 20 percent in the economically developed countries.^[5]^

Percutaneous nephrolithotomy (PCNL) is a kind of minimally invasive procedure, which has been extensively utilized in the treatment of kidney stones.^[6,7]^ It is still a gold standard for treating the kidney stones due to it has less morbidity and invasion than open surgery. Nevertheless, PCNL can lead to the pain after operation and pelvicalyceal system distension owing to the inserted nephrostomy. Many approaches, such as epidural analgesics, non-steroidal anti-inflammatory drugs, and systemic opioids, have been developed to relieve pain, decrease the related complications, hospitalization and medical costs.^[8,9]^ Nevertheless, these approaches may lead to serious adverse reactions, for instance, nausea and vomiting, sedation, respiratory depression, kidney problems, and constipation, particularly in the elderly patients.^[10]^ In a variety of surgeries, paravertebral block is a successful approach of local analgesia.^[11]^ It can generate sympathetic, somatosensory and unilateral block by injecting local anesthetics into paravertebral space containing the thoracic spinal nerves and its branches. The former studies have demonstrated its analgesic effect in abdominal surgery, breast surgery, and thoracotomy.^[12–14]^ At present, there is insufficient evidence for the conventional clinical application of paravertebral block in the PCNL, and some investigations have explored the safety and effectiveness of the paravertebral block in these patients. Therefore, we perform this randomized controlled study protocol to assess the effectiveness of paravertebral block for the PCNL patients.

## Methods

2

This study will be implemented from May 2021 to March 2022 at Affiliated Hospital of Youjiang Medical University for Nationalities. The experiment was granted through the Research Ethics Committee of Affiliated Hospital of Youjiang Medical University for Nationalities (No. 60192038) and recorded in research registry (researchregistry6259). Sequence of random numbers is generated by a computer. Sequentially numbered sealed opaque envelopes are used for the concealment of random numbers. All the patients taking part in our experiment are randomly assigned into the study group and the control group, and each group includes 50 patients.

### Inclusion and exclusion criteria

2.1

This study includes a total of 100 patients. The criteria for inclusion of patients involves:

1.patients over 60 years old;2.American Society of Anaesthesiologists I or II classification.

The criteria for exclusion involves:

1.skin infection at injection site, spinal deformity, abnormal coagulation function;2.patient refusal, and known drug allergy.

### Outcomes

2.3

The visual analogue score, heart rate, the diastolic and systolic blood pressure, complications, side effects, the consumption of opioid and extra analgesic needs are recorded in rehabilitation room 1 hour after the surgery and in the first 24 hours of urological service. At rest, the pain scores are assessed on the basis of visual analogue scale for pain (in which 0 cm represents no pain; while 10 cm represents the most severe pain).

### Statistical analysis

2.4

Through utilizing the Microsoft Excel 2013, the data is recorded, and the analysis of all the data is carried out through utilizing the software of IBM SPSS Statistics for Windows, version 20 (IBM Corp., Armonk, NY, USA). All the data are represented via the proper characteristics, for instance, median, mean and percentage. The categorical variables and continuous variables are respectively analyzed using independent *t* tests and χ^2^-tests. *P* value less than .05 indicates that there is statistical significance.

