## Results

3

Table 1 shows the postoperative data among 2 groups.

**Table 1 T1:** The postoperative data among 2 groups.

Variables	Paraventric block group (n = 50)	Control group (n = 50)	*P* value
Postoperative pain score at 4 hours			
Postoperative pain score at 12 hours			
Postoperative pain score at 24 hours			
Total opioid consumption			
Postoperative complications			
Length of stay			

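### Section 2.4 pairs the tests with the wrong variable types: as written, continuous outcomes get chi-square tests and categorical outcomes get t tests

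*Protocol article*

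**What the plan says.** Section 2.4 of the protocol article gives one rule for choosing a test: "The categorical variables and continuous variables are respectively analyzed using independent *t* tests and χ^2^-tests". It also sets a significance threshold of 0.05 and mentions medians, means and percentages as summaries, without tying any of them to a variable.

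Table 1 in the Results section is an empty shell with a P value column and six rows. Three are pain scores, beginning with "Postoperative pain score at 4 hours" and followed by 12 and 24 hours. The others are "Total opioid consumption", complications, and "Length of stay". Section 2.3 (Outcomes) defines pain on a visual analogue scale (VAS), "in which 0 cm represents no pain; while 10 cm represents the most severe pain". On size, the Methods section says that "each group includes 50 patients".

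**The concern.** Read in order, the sentence lists categorical then continuous variables, and t tests then chi-square tests. Both pairings are the reverse of what the tests are built for.

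A chi-square test on a 0 to 10 cm score treats every distinct value as an unordered category. It takes no account of one score being higher than another, or by how much. It asks whether the two distributions differ in any way, not whether one arm has less pain. With 100 patients spread over many values, the expected counts also become small.

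The question the trial sets out to answer is whether the block relieves pain, and this is the only stated rule for producing the P values on which that answer would rest. An analysis plan that paired the tests correctly would contradict the published protocol. A reader checking the final report against this article could not tell a correction from a post hoc choice.

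**Working it through.** **1. Reach of the rule.** Table 1 rows by type:

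| Row | Type | Test as written |
|---|---|---|
| Pain, 4 h | continuous | chi-square |
| Pain, 12 h | continuous | chi-square |
| Pain, 24 h | continuous | chi-square |
| Opioid consumption | continuous | chi-square |
| Length of stay | continuous | chi-square |
| Complications | categorical | t test |

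Five of six rows get chi-square on a continuous variable. Heart rate and blood pressure in section 2.3 would too, although they are not in Table 1.

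**2. What chi-square does with continuous data.** No assumed effect size is needed here.

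- *All 100 values distinct.* Each of the 100 columns holds one patient, and the expected count is 0.5 per arm. Each column contributes 0.5²/0.5 + 0.5²/0.5 = 1, so the statistic is 100 on 99 degrees of freedom and P = 0.45. This holds even when every patient in one arm scores below every patient in the other.
- *Equal means, different spread.* One arm has 25 patients at 2 and 25 at 6; the other has 50 at 4. Both means are 4. The columns contribute 25 + 25 + 50 = 100 on 2 degrees of freedom, so P < 0.001. The t test gives P = 1.

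**3. Illustrative power for the pain score.** The article states no effect size, SD, power or recording step, so there is no figure to reproduce.

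- From the article: 50 per arm, threshold 0.05 (taken as two-sided, which is not stated), scale 0 to 10 cm.
- Assumed: normal scores kept within 0 to 10, control mean 4 cm, SD 1.5 or 2.0 cm, true difference 0, 1.0 or 1.5 cm, scores rounded to 1, 0.5 or 0.1 cm.
- Method: 4,000 simulated trials per setting, so the Monte Carlo standard error is at most √(0.25/4000) = 0.8 percentage points.

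Check of the t test by formula, power ≈ Φ(δ / (SD·√(2/50)) − 1.96), for a 1.0 cm difference:
- SD 2.0: 1/0.4 − 1.96 = 0.54, power 0.705
- SD 1.5: 1/0.3 − 1.96 = 1.37, power 0.915

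Simulated results (ranges run over the two SDs):

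| Recording step | Type I error, chi-square | Power at 1.0 cm, chi-square | Power at 1.0 cm, t test | Power at 1.5 cm, chi-square | Power at 1.5 cm, t test |
|---|---|---|---|---|---|
| 1 cm | 3% to 4% | 27% to 54% | 68% to 90% | 65% to 94% | 95% to 99.9% |
| 0.5 cm | about 3% | 15% to 32% | 70% to 91% | 43% to 79% | 96% to 99.7% |
| 0.1 cm | 0.2% to 0.4% | 1% to 2% | 69% to 91% | 3% to 9% | 96% to 99.9% |

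The t test's type I error was 4.4% to 5.5%. The share of score levels with an expected count below 5 was 43% to 51% at 1 cm steps and essentially all at 0.1 cm steps (about 48 to 55 distinct values).

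**4. The categorical row.** If complications are yes/no, compare the t test on 0/1 values with the uncorrected chi-square (example counts, not from the article):
- 12/50 v 4/50: pooled proportion 0.16, variance 0.16 × 0.84 × 2/50 = 0.005376, statistic 0.16²/0.005376 = 4.76. Chi-square P = 0.0291, t test P = 0.0292.
- 10/50 v 5/50: chi-square P = 0.161, t test P = 0.165.

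**The case against.** The strongest reply is that this is a transposed word pair. The sentence names the two standard tests and the two standard variable types, and the article has other language slips, such as several different names for the paravertebral space. On that view nobody would run chi-square on raw pain scores, and the harm is hypothetical. This stands as an account of the likely cause, and it makes every consequence above conditional on literal use. It does not make the rule right. Nor can the error be left to an unseen analysis plan: that defence covers detail an article omits, and here the article states a rule.

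A reader might infer that the trial could not detect a pain difference. The documents do not support that. They do not give the recording step. With 1 cm steps, literal chi-square keeps 27% to 54% power for a 1.0 cm difference and 65% to 94% for 1.5 cm. Only recording in 0.1 cm steps brings power close to zero.

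A reader might also infer an excess of false positives. In the settings examined, with identical distributions in both arms, the test is conservative.

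On the categorical side, a t test loses its meaning only for unordered outcomes with several categories, and the article does not say that complications will be coded that way.

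**Conclusion.** Wrong as written. Section 2.4 reverses the tests, and no other part of the article puts them right. The finding rests on the wording and on the count of five continuous rows in six, all three pain rows among them; it does not depend on the simulation.

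If the rule is applied literally, the pain comparison becomes insensitive and stops testing a difference in means. The loss for a 1 cm difference is from about 68% to 91% power down to about 27% to 54% (1 cm steps) or 1% to 2% (0.1 cm steps). These figures are illustrative, because the control mean, SDs, differences and recording steps are all assumed. The reversal matters little for complications if they are yes/no.

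**What to change.** Replace the sentence in section 2.4 with: *Continuous variables are analysed with independent t tests (or a rank test such as Mann-Whitney where clearly skewed) and categorical variables with chi-square tests (or Fisher's exact test where expected counts are small).*

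The cost is one sentence of wording. No change is needed to data collection, sample size or conduct. Any separate analysis plan should be checked for the same reversal so that the two documents agree.

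Baseline adjustment of heart rate and blood pressure is not part of this fix. The article does not say that a pre-induction reading is kept as trial data, and its description of intraoperative monitoring does not name heart rate.

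### No outcome is named primary, yet Table 1 provides for six P values, each judged at .05 without multiplicity control, and the conclusion that the block is effective is tied to none of them

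*Protocol article*

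**What the plan says.** - **Objective (Abstract):** "To assess the effectiveness of paravertebral block" in PCNL patients. No measure of effectiveness is attached to it.
- **Outcomes (section 2.3):** one unranked list: "The visual analogue score, heart rate, the diastolic and systolic blood pressure, complications, side effects, the consumption of opioid and extra analgesic needs are recorded". The times given are 1 hour after surgery and the first 24 hours on the urology service. Pain is scored at rest on a 0-10 cm scale.
- **Statistical analysis (section 2.4):** t tests and chi-square tests. The only criterion is that a P "value less than .05 indicates that there is statistical significance". Neither a primary comparison nor a multiplicity rule is given.
- **Results (Table 1, still blank):** a P value column beside six rows. Three are the pain score: "Postoperative pain score at 4 hours", "Postoperative pain score at 12 hours" and "Postoperative pain score at 24 hours". The others are "Total opioid consumption", postoperative complications and length of stay.
- **Conclusion (Abstract and section 5):** the block is called effective, with no added complications. Neither place says which row supports the first statement.

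**The concern.** A confirmatory comparison needs one outcome, or a controlled family of outcomes, fixed in advance as the basis for the claim. Here six comparisons share one uncorrected threshold, and nothing says which of them decides effectiveness. That choice is left open until the data are in, when whichever row falls below .05 can be put forward. The 5% attached to each row is then not the error rate of the trial's conclusion. No later analysis can repair a choice made after seeing the results.

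The three pain rows make this sharper. They measure the same thing in the same patients, yet each has its own P value, so the article does not say what would follow from, say, a difference at 4 hours and none at 12 or 24.

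**Working it through.** The article states no overall error rate, power or sample-size derivation, so there is no figure of its own to reproduce.

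**Inputs from the article.** Threshold 0.05 per test (section 2.4); six rows with a P value, three of them pain scores (Table 1); 50 patients per group (section 2).

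**Assumptions.** Tests are two-sided, since the article does not say. All six rows are tested and there is no true difference on any of them. Correlations between outcomes are not given, so a range of 0.3-0.7 is shown.

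**Step 1. At least one false-positive row, independent tests.**
- Six rows, either direction: 1 - 0.95^6 = 0.265.
- Six rows, favouring the block (0.025 per test): 1 - 0.975^6 = 0.141.
- Three pain rows, either direction: 1 - 0.95^3 = 0.143.
- Three pain rows, favouring the block: 1 - 0.975^3 = 0.073.
- One test, for comparison: 0.05 and 0.025.

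**Step 2. Allowing for correlation.** The five continuous rows (three pain scores, opioid use, length of stay) are given a common correlation, and complications are taken as independent of them. The three pain rows alone use the same correlation.

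| Correlation | Six rows, either direction | Six rows, favouring block | Pain rows, either direction | Pain rows, favouring block |
|---|---|---|---|---|
| 0.3 | 0.248 | 0.127 | 0.136 | 0.068 |
| 0.5 | 0.224 | 0.114 | 0.125 | 0.063 |
| 0.7 | 0.191 | 0.097 | 0.109 | 0.055 |

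Correlation lowers the rates but does not remove the excess. If all six rows, complications included, correlated at 0.8, the rates would be 0.139 in either direction and 0.070 favouring the block.

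**Step 3. What one averaged pain score would do for precision.** With 50 per group, two-sided 5% and 80% power, a t test at one time detects 0.566 SD. For the mean of three scores with within-patient correlation ρ, this is multiplied by √((1 + 2ρ)/3):
- ρ = 0.3: 0.566 × 0.730 = 0.41 SD
- ρ = 0.5: 0.566 × 0.816 = 0.46 SD
- ρ = 0.7: 0.566 × 0.894 = 0.51 SD

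This assumes the same effect at 4, 12 and 24 hours. At ρ = 0.5, an effect present at only two times would have to be 0.46 × 3/2 = 0.69 SD at each of them. An effect at only one time would have to be 0.46 × 3 = 1.39 SD (from the unrounded 0.462). Both are worse than 0.57 SD for a test at a single time where the effect is present.

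**The case against.** The best defence is that this is a condensed article and that an analysis plan may exist elsewhere. That holds for the form of the model, a Holm procedure or an area-under-the-curve summary, whose absence is no finding. It does not hold for the primary outcome, a core protocol element on which both the outcomes and the analysis sections are silent. Nor does it cover what the article does fix, namely one threshold for every test and a table with six P values.

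Four further objections limit the size of the point, and each stands.

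- A reader might infer that a false finding of effectiveness has about a one-in-four chance. The article does not support that: 26.5% counts false positives in either direction, and only those favouring the block could support the conclusion. That chance is at most about 14%.
- A reader might infer that any one significant row is declared sufficient. No section says so; section 2.4 defines significance for a test. The defect is that no section says what is sufficient.
- A reader might count every measure in section 2.3 and reach 40% for ten tests (1 - 0.95^10 = 0.401). Section 2.3 says that these measures are recorded, not that each is tested for effectiveness.
- The six rows are not all measures of analgesia. Complications are a safety outcome, which the conclusion treats separately, and length of stay is indirect. For pain plus opioid use (four rows), the rate favouring the block is at most 1 - 0.975^4 = 9.6%; for pain alone it is 7.3%. Even that is nearly three times the 2.5% of one test.

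**Conclusion.** The concern holds in this form: no outcome is primary, six between-group P values are provided for at an uncorrected .05, and the conclusion of effectiveness is tied to none of them. If all six are tested, the chance of at least one false-positive row is up to about 26%, or about 19-25% with assumed correlations of 0.7-0.3, against 5% for one test. The chance of one favouring the block is up to about 14%, or about 10-13% with correlation, against 2.5%. For the pain rows alone the upper limits are about 14% and 7%.

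The missing primary outcome follows directly from the text. The rates depend on all six rows being tested and on correlations that the article does not give. Using one pain summary instead of three tests is a sensible way to settle the primary outcome, but its gain in precision is conditional, so separate testing by time is not in itself shown to be the weaker choice.

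**What to change.** 1. **Reconcile the assessment times.** Section 2.3 gives 1 hour and the first 24 hours; Table 1 gives 4, 12 and 24 hours. Until they agree, a pain outcome over the scheduled times is undefined.
2. **Name one primary outcome before any results are seen**, and state that it alone decides effectiveness. One option is resting pain over the Table 1 times, summarised as each patient's mean or area under the curve and compared once at two-sided 5%. The overall error for the claim is then 5%.
3. **Report the individual pain time points** as mean differences with 95% confidence intervals.
4. **Label the other outcomes secondary**, unable to support the claim alone, or test them by Holm. Report complications as safety.
5. **Tie the conclusion to the primary outcome.**

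The cost is protocol wording; a t test on a per-patient summary uses scores already in Table 1 and software already named. The statistical downside is that averaging loses power if the effect is confined to one or two times, which is conceivable because section 2.2 describes the block as given once, before surgery. If a short-lived effect is expected, a single pre-specified time point is an acceptable primary outcome.

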## Results

3

Table 1 shows the postoperative data among 2 groups.

**Table 1 T1:** The postoperative data among 2 groups.

Variables	Paraventric block group (n = 50)	Control group (n = 50)	*P* value
Postoperative pain score at 4 hours			
Postoperative pain score at 12 hours			
Postoperative pain score at 24 hours			
Total opioid consumption			
Postoperative complications			
Length of stay			

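### The article already concludes that the block adds no complications, but Table 1 is empty and a non-significant P value with 50 patients per arm could not support that conclusion

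*Protocol article*

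**What the plan says.** The closing sentence of the protocol article, in both the Abstract and section 5 (Conclusion), compares the block with traditional analgesia and states that "no additional complications are encountered".

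Section 3 (Results) holds one table, with 50 patients in each column and every cell blank. It has a row "Postoperative complications" and a row "Length of stay". The only comparative column is the P value.

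Section 2.4 (Statistical analysis) gives one decision rule: a P "value less than .05 indicates that there is statistical significance". It sets no margin for acceptable excess harm and mentions no confidence interval.

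Section 2.3 (Outcomes) lists complications and side effects among the variables "recorded in rehabilitation room 1 hour after the surgery and in the first 24 hours of urological service". No other recording window for complications is given.

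Section 4 (Discussion) ends with a general remark that further study is needed because of the number of patients. It does not mention safety.

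**The concern.** The safety conclusion is comparative, is written as a finding, and precedes any data. When Table 1 is filled in, the only result that bears on the sentence will be a P value for complications. If that value exceeds .05, nothing in the article prevents the sentence from standing as it is.

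With 50 patients per arm, a non-significant result is compatible with a clinically important excess. Section 2.2 describes needle placement in a space bordered by the pleura, and section 2.1 restricts entry to patients over 60. Readers deciding whether to adopt the block would take the sentence as evidence of safety.

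The recording window adds to this. An event after the first 24 hours on the ward but before discharge falls outside the only window stated, whereas the conclusion carries no time limit.

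**Working it through.** **Inputs from the article.** Patients are "randomly assigned into the study group and the control group, and each group includes 50 patients" (Methods), 100 in total. The significance level is .05, taken as two-sided because the article does not say. For the test, section 2.4 says "The categorical variables and continuous variables are respectively analyzed using independent" *t* tests and chi-square tests. Read literally, that sends categorical variables to the *t* test, so I assume chi-square was meant for complications, and I show Fisher's exact test beside it.

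**Inputs not in the article.** No complication rate, effect size, power or margin is given, so there is no stated figure to reproduce. All rates below are assumptions, shown as a range.

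**Step 1: power.** For control rate p₀ and block rate p₁, power is the sum over all pairs (x, y) of Bin(x; 50, p₁) × Bin(y; 50, p₀), counting only pairs for which the test gives P < .05. The chi-square test is uncorrected.

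| Control v block | Ratio | Chi-square | Fisher |
|---|---|---|---|
| 2% v 4% | 2 | 5% | 1% |
| 5% v 10% | 2 | 14% | 6% |
| 10% v 20% | 2 | 30% | 19% |
| 20% v 40% | 2 | 60% | 52% |
| 2% v 6% | 3 | 14% | 3% |
| 5% v 15% | 3 | 39% | 24% |
| 10% v 30% | 3 | 73% | 64% |

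A doubling is usually missed at control rates of 2% to 10%. A tripling is mostly missed only at control rates near 5% or below.

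**Step 2: what a non-significant table could look like.** The chi-square statistic is (x/50 − y/50)² / [p(1 − p) × 2/50], with p = (x + y)/100 and critical value 3.84.

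- 7 v 2 events: 0.10² / (0.09 × 0.91 × 0.04) = 3.05, not significant.
- 8 v 2 events: 0.12² / (0.10 × 0.90 × 0.04) = 4.00, significant.

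So 14% against 4% would give P > .05. The Newcombe 95% interval for that difference of 10 points runs from −1.8 to +22.5 points.

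**Step 3: equal counts.** With 5/50 in each arm, the Wilson 95% limits for each arm are 4.3% and 21.4%. The Newcombe half-width is √[(0.100 − 0.0435)² + (0.2136 − 0.100)²] = √(0.0032 + 0.0129) = 0.127. The interval is −12.7 to +12.7 points.

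**Step 4: no events.** With 0/50 in the block arm, the exact two-sided 95% upper limit is 1 − 0.025^(1/50) = 7.1%. A complication with a true rate of 1% would be missed altogether with probability 0.99^50 = 61%.

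**Step 5: the window.** Section 2.3 gives 1 hour after surgery and the first 24 hours on the urology ward. Table 1 reports length of stay, which cannot be filled in without the date of discharge. Every patient's record must therefore be opened at discharge, but complications are not stated to be collected then.

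**The case against.** **The document never says that P > .05 will be read as safety.** This is right. A reader might infer that the conclusion rests on a significance test, but Table 1 is blank, so at present it rests on no data at all. The point is limited to this: the sentence is already written, the P value is the only comparison planned that could bear on it, and that comparison could not support it.

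**A non-significant result is not to be expected for every doubling or tripling.** Also right. A reader might infer that 50 per arm would miss any such increase. At 20% v 40% chi-square power is 60%, and at 10% v 30% it is 73%. The Discussion's list of problems after this surgery includes nausea, vomiting, urinary retention and sleep disorders, so a low overall rate cannot be presumed.

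**The window may not be exhaustive.** Section 2.3 does not list length of stay, yet Table 1 reports it, and the complications row names no window. So the documents do not establish that later complications will go uncounted. What stands is that the only stated window ends at 24 hours on the ward and the conclusion is not limited to it.

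**Low power for complications is ordinary in an analgesia trial of 100 patients, and interval methods can be left to an analysis plan.** Accepted. Neither the sample size nor the absence of a named interval method is the fault. The fault is a stated comparative safety conclusion that the stated design cannot deliver.

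**The Discussion admits the limitation.** Only in part. Its remark on patient numbers is not tied to complications, and the unqualified conclusion follows it.

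**Conclusion.** The point holds in limited form. The statement that the block brings no additional complications has no data behind it, and a non-significant P value with 50 patients per arm would not supply the missing support. For assumed control rates of 2% to 10%, chi-square power to detect a doubling is about 5% to 30%, and Fisher's test does worse. Even the most reassuring results leave room for a material excess: ±12.7 points with five events in each arm, or a block-arm rate of up to 7.1% with none.

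The power figures depend on assumed rates, a two-sided .05 level and a chi-square test, and they become less severe as the control rate rises. The unsupported sentence does not depend on these assumptions. The window is a secondary matter: as stated, it would support a conclusion about the first 24 hours only.

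**What to change.** 1. Withdraw the safety sentence from the Abstract and from section 5 until there are data.
2. In Table 1, give complication counts per arm and the risk difference with a 95% confidence interval (Newcombe is suitable at these counts). List block-related events separately, with an exact confidence interval for the block arm.
3. State in section 2.4 that a non-significant difference in complications will not be reported as absence of additional complications.
4. In section 2.3, extend the recording of complications and side effects to hospital discharge, or restrict any safety statement to the first 24 hours.

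The cost is a change of wording and, for the extension to discharge, completing the complications record once more at a point where length of stay must be noted anyway. No extra patients or visits are needed. The drawback for the sponsor is a wider and less favourable safety statement.
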